### Ethical consideration

GP investigators must recommend that all patients who are consulting for antihypertensive prescription consider participating in this study, without conducting any selection of patients to be approached or not. The participating patients will give their written informed consent after being told about the study. Their participation or refusal will not affect their medical and nursing care.

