**Methods/design:**

We will conduct a cluster randomised controlled stepped wedge trial, with eight clusters of 10 general practitioners each. The physicians will suggest to all of their antihypertensive-treated patients that they take part in this study. The InPAct program will be implemented in the clusters in random order along five successive three-month periods. Two new clusters will be trained in implementing the program at each step. The program features: an interactive patient booklet including informative paragraphs, several care plans and adverse drug event report forms; and standardised training of physicians in how to present the booklet to the patient. The primary outcome will be the reporting of adverse drug events by patients to their physician within three months. We assume that the number of patients reporting at least one adverse drug event will increase from 3% before program implementation to 7.5% afterward (coefficient of variation = 0.5, α = 0.05, β = 0.2), which means that 1,200 patients must be included. The effect of the intervention on the main outcome will be quantified and tested using a mixed logistic model to integrate cluster and time effects.

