### Recruitment of patient participants

GP investigators involved in the study are required to recommend participation in this study to each patient over 18 years old who is consulting to initiate, modify or renew an antihypertensive drug prescription. In order to be included, the patients must meet the inclusion criteria, understand the investigator’s language, and agree to answer a telephone survey at home. Only the patients included in the study after the entry of their GP into the intervention group will receive the interactive booklet. Each patient will be followed during three months, with the outcome criteria collected at the end of this period.

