### Sample size

Sample size calculations were carried out using the method implemented by Hussey and Hughes [20]. In our study, the number of clusters was fixed at eight, and the number of time periods was fixed at five. The expected effect of the intervention is an absolute increase of 4.5% of the percentage of hypertensive patients who will report at least one ADE; *i.e.*, an increase from 3% in the group without intervention to 7.5% in the group with intervention. The clustering induces an increase in the variance of the outcome criterion, due to inter-cluster heterogeneity; this increase is quantified by the inter-cluster coefficient of variation. For a given number of patients per cluster, the power of the study was calculated for different coefficients of variation between 0.1 and 0.5, which corresponds to the range of values usually observed. The inclusion of 240 patients per time period (30 patients per cluster) leads to a power greater than 80% regardless of the coefficient of variation (Table 1). The type I error was fixed at 5% for a bilateral test. In the context of the InPAct study, for logistical reasons and to avoid the risks of inter-cluster contamination and clusters with no inclusion, it was preferable to limit the number of GP clusters. With a classic CRCT parallel group design, the number of patients to include would have to be at least 6,000 to maintain a statistical power of 80% with 12 clusters (under 12 clusters it is impossible to reach a statistical power of 80%, regardless of the number of patients), but with our choice of stepped wedge design, the patient number decreases to 1,200 for eight clusters with a statistical power of 80%.

**Table 1 T1:** Statistical power calculated from the coefficient of variation and number of patients per time period

**Cv**	**184 patients per time period**	**208 patients per time period**	**240 patients per time period**
0	0.80	0.85	0.89
0.1	0.80	0.84	0.89
0.2	0.78	0.83	0.87
0.3	0.76	**0**.**81**	0.85
0.4	0.74	0.78	0.83
0.5	0.72	0.76	**0**.**81**

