### Randomisation

Before the beginning of the implementation phase, clusters were randomly allocated a time when they are to be given the intervention. In agreement with the CONSORT statement extended to cluster randomised trials, the team of statisticians, which was blinded to the identity of the clusters, randomised the clusters using computer generated random numbers [21]. The randomisation sequence was therefore established before the beginning of program implementation. Only the research team was aware of the allocation of all of the clusters. In order to maintain allocation concealment, GPs will be informed of their allocation time only in the month prior to the date of implementation in their cluster. This one-month delay is necessary for the organisation of their training for the InPAct program.

It is impossible to blind patients and GP participants for the intervention, due to the nature of the intervention, *i.e.*, training GPs in the distribution of a booklet to patients. Outcome assessment will, however, be essentially blinded. Indeed, most of the data are collected in a blinded fashion by clinical research associates, whereas the only non-blinded medical data will be those collected by the GPs.

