### Statistical analysis

The quantitative characteristics of the patients included during the control and intervention periods will be described either by using the mean and the standard deviation, or by using the quartiles and the minimum and maximum values, depending on the shape of the distribution. The qualitative characteristics of the patients will be described using the absolute and relative frequencies in the different categories. The comparisons between the two groups will be carried out using a student-*t* test or a non-parametric test for the quantitative characteristics and a chi-squared test or a Fisher’s exact test for the qualitative characteristics.

A stepped wedge design is a unidirectional crossover trial. The particularity of this design, in comparison with traditional crossover studies, is that the information allowing quantification and testing of the intervention effect is present within and between the clusters. As recommended by Hussey and Hughes [20], the analysis of the intervention effect on the main outcome will be carried out using a mixed logistic model with a random intercept, in order to take into account the within-cluster correlation, to use both within-cluster and between-cluster information, and to take into account any evolution of the intervention effect over time. The mixed logistic model may be used to analyse a cluster randomised trial even when the number of clusters is small, as long as the number of patients per cluster is greater than approximately 30, which is the case in our study. Austin showed that the estimation of the regression coefficient, which quantifies the intervention effect, preserves good properties in terms of bias and coverage probability of the confidence interval, if the number of subjects per cluster is over 30, and even if the number of clusters is as few as five [22]. This analysis will be carried out using the lme4 package of the most recent version of the R software.

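### Unblinded GPs enrol new patients in each phase, but the planned control-versus-intervention tests ignore cluster and period, and the stated primary model would absorb a case-mix shift at the switch

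*Protocol article*

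**What the plan says.** **Who is approached.** Under Recruitment of patient participants, GPs are "required to recommend participation in this study to each patient over 18 years old". The rule reaches anyone of that age "who is consulting to initiate, modify or renew an antihypertensive drug prescription". The Ethical consideration section repeats that this is done "without conducting any selection of patients to be approached or not".

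**How many.** The abstract describes a design "with eight clusters of 10 general practitioners each". The Sample size section gives the size as "240 patients per time period (30 patients per cluster".

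**What the recruiter knows.** The Randomisation section says that neither GPs nor patients can be blinded, and that "GPs will be informed of their allocation time only in the month prior to the date of implementation in their cluster". New patients are enrolled in both phases, and only those included after their GP has switched receive the booklet.

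**How the patient groups are compared.** Statistical analysis first plans descriptive summaries for control-period and intervention-period patients. It then says: "The comparisons between the two groups will be carried out using a" Student t or non-parametric test for quantitative characteristics, and a chi-squared or Fisher test for qualitative ones. Neither cluster nor period appears.

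**How the primary outcome is modelled.** Statistical analysis gives a mixed logistic model with a random intercept. The abstract says that it covers cluster and time effects. Under Data collection, clinical data and the prescription are entered in the e-CRF at inclusion.

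**The concern.** In a stepped wedge trial that enrols new patients in each period, randomising the order of clusters does not protect the comparison from changes in who is enrolled. Here the person who proposes the study also delivers the intervention and knows the current phase, and the consenting patient is unblinded too. If the patients included after the switch are more inclined to report an adverse drug event, reporting rises without any effect of the program.

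Two parts of the stated analysis bear on this. The group comparison should show whether case mix differs, but the named tests assume independent patients, and in this design control data are early and intervention data late. Their p-values can therefore signal imbalance where there is none. The primary model, as stated, removes stable cluster differences and common calendar effects, but not a change in patient mix that happens when each cluster switches.

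**Working it through.** **1. The plan's own figure.** Inputs from Sample size: 8 clusters, 5 periods, 3% versus 7.5%, two-sided 5%, Cv 0.5. From Study design: two clusters cross at each step. The Hussey–Hughes weighted least squares calculation was run with fixed period effects, residual variance 0.03 × 0.97, between-cluster SD 0.5 × 0.03 = 0.015 and 30 patients per cluster-period. It gives power 0.817, against 0.81 in Table 1. Over all 18 cells of the table the largest gap is 0.009. So 30 per cluster-period is the design figure.

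**2. Patients per GP.** 8 × 10 = 80 GPs; 240/80 = 3 per GP per three-month period; 1,200/80 = 15 per GP over the trial.

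**3. Error rate of the unclustered tests.** Each condition has 20 cluster-periods, so 20 × 30 = 600 patients. A cluster's weight in the raw mean difference is its share of the intervention patients minus its share of the control patients:

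- Unit 1 (1 control, 4 intervention periods): 120/600 − 30/600 = 0.15
- Unit 2: 90/600 − 60/600 = 0.05
- Unit 3: −0.05
- Unit 4: −0.15

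With two clusters per unit, the squared weights sum to 2 × (0.0225 + 0.0025 + 0.0025 + 0.0225) = 0.10. For a characteristic with total variance 1, the variance of the difference is

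0.10 × ICC + 2(1 − ICC)/600,

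whereas the test uses about 2/600. With R the ratio of the two, the actual rejection rate is 2[1 − Φ(1.96/√R)]. The article gives no ICC for patient characteristics, so the values are assumed:

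| ICC (assumed) | Variance ratio R | Rejection rate, no true imbalance |
|---|---|---|
| 0.01 | 1.29 | 8.4% |
| 0.02 | 1.58 | 11.9% |
| 0.05 | 2.45 | 21.0% |

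A separate simulation of the t-test on the 8 × 5 × 30 layout (4,000 runs each) gave 5% at ICC 0, 9% at 0.01, 21% at 0.05 and 32% at 0.10.

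**4. Calendar drift.** Counting P1 as 0, the mean period is (0×8 + 1×6 + 2×4 + 3×2)/20 = 1 for control patients and (1×2 + 2×4 + 3×6 + 4×8)/20 = 3 for intervention patients. An assumed drift of 0.05 SD per period thus becomes a raw difference of 0.10 SD. At ICC 0.05 the simulated rejection rate rises to 44%. The primary model's time effect already deals with such drift, so this signal says nothing about selective enrolment.

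**5. What a case-mix shift at the switch could do.** Assume no program effect and 3% reporting in the control phase. A share q₀ of control patients, and q₁ of intervention patients, report k times as often as the rest. The intervention-phase rate is then 0.03 × [1 + q₁(k − 1)]/[1 + q₀(k − 1)].

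- k = 2, share 30% to 40%: 0.03 × 1.4/1.3 = 3.2%, about 5% of the 4.5-point target
- k = 3, share 25% to 50%: 0.03 × 2.0/1.5 = 4.0%, about 22%
- k = 4, share 30% to 50%: 0.03 × 2.5/1.9 = 3.9%, about 21%

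A shift that follows each cluster's own switch has the same pattern over cluster and period as the intervention indicator. A random intercept and time effects cannot separate the two.

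**The case against.** The strongest reply is that the article forbids selection twice, keeps the switch date from GPs until a month before, and has every cluster contribute to both conditions. The model removes stable differences between clusters and covers time. The group comparisons are descriptive: no decision hangs on them and they do not enter the effect estimate. Covariate lists and screening logs usually sit in a full protocol or SAP, and neither is shown.

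Most of this stands. A reader might infer that 3 patients per GP per quarter cannot be squared with approaching everyone, and that GPs must therefore choose. The article does not support that. The 240 per period is a required size and not a cap, no number of eligible patients per GP is given, and inclusion also needs written consent, command of the investigator's language and agreement to a telephone survey. The share of eligible patients that 3 represents is unknown: 15% if a GP sees 20 in a quarter, 3% if 100, both assumed. Nor is the absence of a screening log from an article a defect.

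Two things remain. Differential enrolment needs no breach of the rule, since consent is given by unblinded patients to unblinded GPs. And the tests are written into the current text: they are wrong for this design whatever an SAP may add, even though they do not feed the primary result.

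**Conclusion.** The point holds in limited form. The tests named for comparing control-period with intervention-period patients are not valid in this design: a nominal 5% test rejects in about 8% to 21% of trials for assumed ICCs of 0.01 to 0.05, and more often if case mix drifts with time. Separately, enrolment by unblinded GPs leaves room for a case-mix shift at the switch. The primary model as stated, with cluster and time only, would count such a shift as intervention effect.

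The size of that bias is not known. The 5% to 22% of the planned effect is illustrative and rests wholly on assumed reporting ratios and shifts. Nothing here shows that GPs select patients or that the trial's result will be biased. The change is worth making because it is specific, and because the Trial status section says that analysis had not begun at submission.

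**What to change.** In the Statistical analysis section:

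1. Remove the t, non-parametric, chi-squared and Fisher tests between conditions. Keep the descriptive summaries by condition or, if a formal comparison is wanted, take it from a model with a cluster random effect and period.
2. Add to the mixed logistic model a small, prespecified set of baseline variables from the clinical and prescription data entered at inclusion, either as the primary analysis or as a named sensitivity analysis. Age and number of drugs are examples; add prescription type (initiate, modify, renew) if it is recorded, which the article does not say.

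**Cost.** Slightly more analysis work, and an odds ratio that is conditional on the covariates. The list must be short: at the planned rates about 600 × 0.03 + 600 × 0.075 = 18 + 45 = 63 patients would report an event, and the model must also estimate time effects. Adjustment deals only with measured differences.

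A rule limiting each GP to the first three consecutive patients is not advised. Enrolment has begun, so a new rule would itself change case mix at a calendar point, and intervention data are concentrated in later periods. It would also cap each cluster-period at 30 with no reserve: at Cv 0.5, Table 1 gives power 0.81 with 240 per period and 0.76 with 208.

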### Trial status

The InPAct study is funded by the French National Program for Hospital Clinical Research. The study protocol was reviewed and approved on June 28, 2011, by the Hospital Ethics Committee. All procedures are in accordance with the Declaration of Helsinki. The InPAct study has been registered as a clinical trial (Current Controlled Trials NCT01610817). The enrolment of patients has begun, but data cleaning or analysis had not yet begun as of this article’s submission.

## Discussion

This article has outlined the design and method of data collection for the InPAct study, as well as details on the implementation of the intervention. The aim of this study is to evaluate how effectively the InPAct program encourages patient-GP interaction and improves patient-initiated ADE reporting. This is the first randomised controlled study that combines a patient education program and a patient reporting system for ADEs with the aim of improving patient safety in primary care.

### Originality of the InPAct program

The InPAct program is a patient safety and patient education intervention that has been developed and evaluated through successive qualitative and quantitative studies as recommended by the Medical Research Council [23]. The implementation of the InPAct program may increase ADE reporting by patients in general practice. In order to improve communication, the InPAct program will encourage GPs to ask their patients about their condition, their antihypertensive prescription drugs, their other healthcare prescriptions, and their experience with ADEs. The GP will inform the patient about the benefits and risks of antihypertensive prescription drugs. The patient will be encouraged to participate actively in his care by writing a care plan and in his own safety by detecting and describing ADEs using the report form included in the InPAct booklet. The GP will analyse patient reports to establish what role, if any, a particular drug may have played in the onset of an ADE. It is expected that the detection of ADEs and their description in report forms by patients will promote the implementation of corrective and preventive actions to reduce the occurrence of ADEs and their complications in general practice. Interventions to improve drug management in general practice have already been tested. Weingart et al. have shown in an observational study that the reception of an automatic email with information about ADE interactions and allergies within the first 10 days of a new prescription can improve communication between a patient and his GP [24]. Roughead et al. have demonstrated that educational materials for GPs and patients can improve the verification of the prescription by patients at home [25]. Fick et al. have shown that an educational booklet with a list of inappropriate medications for the elderly can improve a review of prescriptions by GPs [26]. In these general practice intervention studies, however, patients were not encouraged to participate actively in their care, and professional practice was assessed instead of patient outcomes.

A program combining both oral and written information can foster improved communication between a patient and his GP. Such a program can also provide patients with enhanced skills for participating in their own care. It has been shown that information leaflets can improve antibiotic use for respiratory tract infection care management in general practice [27], and that self-management leaflets and booklets for minor illness can reduce the number of inappropriate consultations [28]. Moreover, educational leaflets and questions on knowledge about contraception [29] or hypertension [30] can improve not only patient knowledge, but also patient compliance. Finally, we have identified only one study that has demonstrated the effectiveness of patient education in reducing the frequency of ADE occurrence [31]. We have not identified other educational patient programs that have shown a statistically significant improvement in ADE prevention. None of these studies featured a combination of a patient education program and a patient reporting system for ADEs that aimed to prevent ADEs and reduce their associated complications.

### Advantages of the stepped wedge design in the particular context of a study in general practice

The stepped wedge trial design used in this study is a particular form of cluster randomised controlled design that is especially useful for the evaluation of patient safety programs in general practice. Findings from such a study design have been shown to generate sound scientific evidence and may make it easier to implement complex health interventions. The CRCT stepped wedge design can prove the effectiveness of an intervention with more robustness than can non-randomised designs, in particular in the case of routine implementation. This design is particularly relevant when for logistical, practical or financial reasons, it is difficult to deliver the intervention simultaneously to all of the clusters [15-17].

First, in the InPAct study, it was inappropriate to use individual randomisation of patients, because GPs must be trained in the intervention (InPAct program). We therefore used cluster randomisation of GPs belonging to the same office or network of knowledge or care in order to avoid contamination bias. Second, it was difficult to use a parallel design as in a classic CRCT. Indeed, for logistical reasons, and because the workload and availability of GPs can be adversely affected at certain times of the year (due to winter epidemics, seasonal allergies, or high demand for back-to-school medical certificates in September), it was difficult to implement the program to all GPs simultaneously in the InPAct study. One advantage of the stepped wedge design is that the program will be introduced to GPs sequentially in the order assigned by randomisation. So, only some GPs must be trained simultaneously in the presentation of the booklet, over a particular time period. Third, since we obtained no arguments in favour of an adverse effect of the InPAct program during the pilot study [18], and since all GPs will eventually receive the intervention (which is a characteristic of the stepped wedge design versus a classic CRCT design), GPs are motivated to continue their participation until study’s end.

There are also statistical advantages to choosing a CRCT stepped wedge trial. First of all, GPs are their own controls in both control and intervention groups. This improves comparability in both groups. The CRCT stepped wedge design may also require fewer clusters than a CRCT parallel group design to ensure similar group comparability, in terms of population characteristics. This design therefore increases statistical power compared to parallel group design, because the program effect is estimated not only by between-cluster comparisons but also by within-cluster comparisons. This suggests that the use of a stepped wedge design should decrease patient sample size, compared to a classic CRCT parallel group design [17,20,32]. For the InPAct study, the number of patients to be included (1,200) was calculated to be strongly reduced with a stepped wedge design versus a classic CRCT design, in order to maintain the statistical power of 80% and a cluster number of eight. Additionally, the effects of time can be included in our choice of statistical model, which allows temporal changes in the effectiveness of the program to be considered [16,17,20]. Indeed, the opportunities arising from modelling the effects of time can be illustrated by considering the stepped wedge design as a multiple-arm parallel design, in which the research aims not only to assess intervention effects, but also to determine whether time of intervention affects the effectiveness of the intervention. Such time effects can include seasonal variations both in GP practice and in the reporting, occurrence and progression of ADEs. In general practice, the seasonal variability in the workload of GPs may negatively affect both their availability for providing health information and the effectiveness of the intervention for the patient. The behaviour of both GPs and patients could also be influenced by external factors that are independent of the study, such as a public campaign about a reporting system for ADEs. For the patients, diuretic antihypertensive-associated ADEs such as dehydration may be more serious in summer due to high temperatures. Even if including time as a random effect could be an advantage of the stepped wedge design, Hussey and Hughes have suggested that a relatively complex model might be required to take into account the time effect [20].

Finally, the InPAct study will provide additional knowledge about the effects of both an interactive program for GPs and patients, and an ADE reporting system for patients. If the InPAct program is found to be effective in increasing ADE reporting by hypertensive patients and in implementing corrective and preventive actions for improving patient safety in general practice, then this program could be implemented in other regions. Indeed, another advantage of the stepped wedge design is its faculty to test the feasibility of implementing an intervention in a certain number of regions prior to its generalisation. Moreover, other similar programs, using the same levers, could be implemented for other commonly prescribed drugs such as anticoagulants, psychotropics, analgesics, or antibiotics in primary care.

